**Arm Strengthening Exercises**			
**Arm flexors**	Non-weight bearing	Bicep curls	**Instruction:** Stand with back straight and arms by side. Hold a weight (around 500 g) in each hand. Bend one elbow and bring hands towards shoulder, then lower slowly down. Repeat on the other side. **Progression:** Increase resistance.
**Arm extensors**	Weight bearing	Wall push up	**Instruction:** Stand facing a wall with feet shoulder-width apart about 30 from the wall. Place palms on the wall at shoulder height. Slowly bend elbows and lean towards the wall. Slowly straighten elbows to return to starting position. **Progression:** Increase repetitions.

### Diet

Participants in the diet and exercise group will also receive six individual consultations with a dietitian via videoconference over 6 months. The timing of these consultations is recommended in weeks 1, 3, 6, 10, between 14 and 17 weeks, and between 19 and 23 weeks, but will be negotiated between the participant and their dietitian. The first consultation will occur 2–3 days following the first consultation with the physiotherapist and will last for approximately 45 min. The remaining consultations will last approximately 30 min. For each participant, dietitians will individualise a dietary intervention involving a ketogenic VLCD. Our pilot study using a ketogenic VLCD demonstrated high acceptability among people with hip OA [22]. Participants will be encouraged to lose at least 10% of their body weight. Five percent weight loss is recommended for improvement in OA symptoms [8] albeit based on trials in knee OA but a dose response is apparent with greater benefits found for 10% or more weight loss. We have demonstrated that 10% weight loss is achievable in our pilot study using a ketogenic VLCD [22].

Prior to their first consultation, participants will receive via post a variety of Optifast meal replacements (Nestlé Health Science, Rhodes, Australia) equivalent to two meals per day for 1 month and educational materials to support weight loss (Table 1). Participants will receive their preferred Optifast meal replacements over the subsequent 5 months. Participants will be asked to weigh themselves at home weekly to record their weight in their logbook throughout the duration of the trial. The purpose of tracking weekly weight is help to motivate participants.

During the first consultation, a personalised management plan will be developed, including appropriate weight loss goals and target weight. Participants will be asked to replace two meals each day, with Optifast meal replacement products and consume a low-carbohydrate meal consisting of protein (e.g. meat, seafood, eggs or tofu), non-starchy vegetables or salad and a tablespoon of oil/fat (if gall bladder in situ). The diet consists of approximately 800 kcal (3280 kJ) per day. Modifications of the diet will be permitted as necessary. Throughout the remaining five consultations, dietitians will discuss progress and use motivational interviewing principles and techniques to help motivation, self-efficacy and overcome barriers preventing participants completing their weight loss plan. Dietitians will also discuss the resource booklets sent to participants, to help adhere to their weight loss plan such as choosing a support person and planning for unforeseen events.

Once participants achieve at least 10% weight loss, they will choose whether to transition to a weight maintenance phase or continue with the ketogenic VLCD to reduce weight further. The transition phase will last at least 2 weeks and involves reducing meal replacements to one meal per day and reintroducing low glycaemic index carbohydrates. Upon completion of the transition phase, participants will enter the maintenance phase and be asked to consume a healthy diet in accordance with the Commonwealth Scientific and Industrial Research Organisation Total Wellbeing diet of high protein, low glycaemic index carbohydrate and low fat. Participants who regain a minimum of 2 kg or more will be advised to again engage in the ketogenic VLCD for 1–2 weeks. Online consultation notes will be used by dietitians. Participants will have access to meal replacements from enrolment to 6 months at no cost to themselves, after which if they opt to re-engage with the ketogenic VLCD, meal replacements will be self-funded. Long term weight maintenance strategies will be addressed during the program to help participants maintain their weight loss after their dietitian support finishes.

### Physiotherapist and dietitian training

Eight musculoskeletal physiotherapists with experience managing people with hip OA, and current registration with Australian Health Practitioner Regulation Agency will deliver the exercise program. All physiotherapists attended a two-hour training session and were provided with a treatment manual describing the exercise program. Five accredited dietitians, with clinical experience in weight management will deliver the diet intervention. All dietitians will complete i) training in best-practice OA management delivered by researchers; ii) motivational interviewing skills delivered by Health and Wellbeing Training Consultants over 2-days; iii) ketogenic VLCD delivered by researchers via 1-h webinar. Further details on training have been published elsewhere [28]. Telephone meetings will be conducted between the research team, physiotherapists and dietitians to address any study issues that arise.

### Treatment fidelity

Throughout the trial, clinicians will be encouraged to discuss any issues that arise delivering the interventions with the researchers. Treatment notes from consultations will be assessed for dietitian and physiotherapist adherence to trial protocol.

### Outcome measures

Table 3 summarises the outcome measures and assessment time-point for each outcome measure. The primary outcome is overall average hip pain severity in the last week measured on an 11-point numeric rating scale (NRS), where 0 = ‘no pain’ and 10 = ‘worst pain possible’ [34] measured at baseline, 6 months and 12 months. This is a validated measure of pain that has been recommended for use in OA clinical trials [35]. Conclusions regarding efficacy will be based on the 6-month change in our primary outcome.

**Table 3 Tab3:** Outcome summary

Domain	Instrument	Timepoint
**Descriptive measures**		Baseline
Age, sex, height		Baseline
Duration of hip symptoms		Baseline
Geographical location		Baseline
Education level		Baseline
Current employment status		Baseline
Problem in other joints		Baseline
Radiographic disease severity	Kellgren and Lawrence grading scale	Baseline
Comorbidities	Self-Administered comorbidity questionnaire	Baseline
Treatment expectation	5-point ordinal scale	At group allocation
**Primary outcome**		
Overall average hip pain in past week	11-point NRS	Baseline, 6 and 12 months
**Secondary outcomes**		
Weight	Self-reported	Baseline, 6 and 12 months
Body mass index		Baseline, 6 and 12 months
Visceral fat mass	Dual energy x-ray absorptiometry	Baseline and 6 months
Total body fat mass	Dual energy x-ray absorptiometry	Baseline and 6 months
Hip pain	11-point NRS	6 and 12 months
Hip pain, difficulty with activities of daily life, hip-related quality of life	HOOS	Baseline, 6 and 12 months
Health-related quality of life	AQoL-8D	Baseline, 6 and 12 months
Perceived change in physical activity since baseline	7-point ordinal scale	6 and 12 months
Perceived change in hip problem since baseline	7-point ordinal scale	6 and 12 months
**Other measures**		
Total body lean mass	Dual energy x-ray absorptiometry	Baseline and 6 months
Depression, anxiety and stress	Depression, Anxiety and Stress Scale	Baseline, 6 and 12 months
Pain-related fear of movement	Brief Fear of Movement Scale	Baseline, 6 and 12 months
Self-reported medication use		Baseline, 6 and 12 months
Self-reported use of co-interventions		6 and 12 months
Self-control for eating	Weight Efficacy Lifestyle Questionnaire	Baseline, 6 and 12 months
**Adherence**		
Self-rated adherence to physical activity plan	5-point Likert scale	Baseline to 6 months
Self-rated adherence to weight management	5-point Likert scale	Baseline to 6 months
Self-rated number of strengthening exercise sessions completed over past 2 weeks		6 months
Number and duration of consultations with physiotherapist		Baseline to 6 months
Number and duration of consultations with dietitian (diet and exercise group only)		Baseline to 6 months
Number of weeks using meal replacements (diet and exercise group only)		Baseline to 6 months
**Harms**		
Adverse events		6 and 12 months

Secondary outcomesi)Body weight, measured in kilograms. Participants will be asked to use the same set of scales across the time-points;ii)Body mass index, measured in kg/m^2^;iii)Visceral fat mass, measured in grams and percentage of total body mass;iv)Total body fat mass, measured in grams and percentage of total body mass;v)Hip pain, measured as the proportion who meet or exceed the minimal clinical important difference (MCID) in NRS pain (at least 1.8 units of improvement) [36];vi)Hip Osteoarthritis Outcome Scale (HOOS) pain subscale, normalised to 0–100 scale (100 indicating no symptoms and 0 indication extreme symptoms) [37];vii)HOOS activities of daily living subscale, normalised to 0–100 scale (100 indicating no difficulty and 0 indication extreme difficulty) [37];viii)HOOS quality of life subscale, normalised to 0–100 scale (100 indicating better quality of life and 0 indication lower quality of life) [37];ix)Health-related quality of life, measured using the Assessment of Quality of Life Instrument (AQoL-8D) [38];x)Global rating of change in physical activity, scored on a 7-point Likert scale for “change in your physical activity levels since you began the study” from “much less” to “much more”;xi)Global rating of overall change in hip problem, scored on a 7-point Likert scale for “change in your hip problem since you began the study” from “much worse” to “much better” when compared to baseline.

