**Methods:**

One hundred people with symptomatic and radiographic hip OA will be recruited from the community. Following baseline assessment, participants will be randomly allocated to either, i) diet and exercise or; ii) exercise only. Participants in the diet and exercise group will have six consultations with a dietitian and five consultations with a physiotherapist via videoconferencing over 6 months. The exercise only group will have five consultations with a physiotherapist via videoconferencing over 6 months. The exercise program for both groups will include prescription of strengthening exercise and a physical activity plan, advice about OA management and additional educational resources. The diet intervention includes prescription of a ketogenic very low-calorie diet with meal replacements and educational resources to support weight loss and healthy eating. Primary outcome is self-reported hip pain via an 11-point numeric rating scale (0 = ‘no pain’ and 10 = ‘worst pain possible’) at 6 months. Secondary outcomes include self-reported body weight (at 0, 6 and 12 months) and body mass index (at 0, 6 and 12 months), visceral fat (measured using dual energy x-ray absorptiometry at 0 and 6 months), pain, physical function, quality of life (all measured using subscales of the Hip Osteoarthritis Outcome Scale at 0, 6 and 12 months), and change in pain and physical activity (measured using 7-point global rating of change Likert scale at 6 and 12 months). Additional measures include adherence, adverse events and cost-effectiveness.

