### Participants

We will recruit 100 participants with hip OA from metropolitan Melbourne and Sydney through advertisement, print/radio/social media and our research volunteer database. Hip OA will be classified according to the American College of Rheumatology classification criteria (pain in the groin or hip region on most days of the past month and femoral or acetabular osteophytes and joint space narrowing (superior, axial and/or medial) on x-ray) [25]. Participants will be included if they:i)are aged 50 years or older;ii)report a history of hip pain ≥3 months;iii)report an average pain score of at least 4 on an 11-point numeric rating scale (anchored at 0 = no pain, 10 = worst pain imaginable) over the previous week;iv)report pain in the groin or hip region on most days of the past month [25];v)have femoral or acetabular osteophytes and joint space narrowing (superior, axial and/or medial) on x-ray) [25];vi)have access to a device with internet connection;vii)have a BMI > 27 kg/m^2^; based on the Royal Australian College of General Practitioners guideline for obesity management, which indicates usage of a very low energy diet to induce rapid weight loss for those with BMI > 30 kg/m^2^ or those with BMI > 27 kg/m^2^ who also suffer comorbidities such as OA [26];viii)are willing and able to give informed consent and participate fully in the interventions and assessment procedures;ix)have the ability to weigh themselves (e.g. access to scales);x)pass the Exercise and Sports Science Australia stage 1 adult pre-exercise screening system [27] or obtain general practitioner clearance for participation in the study.

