### Randomisation and allocation concealment

Eligible participants will be randomised to receive either i) diet and exercise or ii) exercise. An independent biostatistician has prepared the randomisation schedule (random permuted blocks) stratified by site (Melbourne or Sydney) and sex (male or female). The schedule will be stored on a password-protected website (REDCap) at The University of Melbourne maintained by a researcher not involved in either participant recruitment or administration of outcome measures. Each participant will receive a unique study ID code, and this will be documented in the participant’s record/database in addition to all study documents. Group allocation will be revealed after completion of baseline outcomes.

Although participants will not be informed about the study hypothesis until the study is completed, the participants will be unblinded. Participants will be informed that we are comparing the two interventions (described below) to determine which intervention achieves the most benefits. The primary outcomes and some of the secondary outcomes are participant-reported, so participants are also the assessors. Physiotherapists and dietitians will not be blinded to group allocation or study hypothesis. Staff conducting assessments for some of the secondary outcomes (e.g. body composition) will be blinded. Statistical analyses will be performed blinded.

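### The 6-month weight and BMI comparison rests on self-report by unblinded participants, although blinded DXA at the same visits should supply a total mass

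*Protocol article*

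**What the plan says.** The abstract of the protocol article lists "self-reported body weight (at 0, 6 and 12 months) and body mass index (at 0, 6 and 12 months", and Table 3 gives self-report as the instrument for weight. Table 3 leaves the instrument for BMI blank. The list of secondary outcomes under Outcome measures adds: "Body weight, measured in kilograms. Participants will be asked to use the same set of scales across the time-points". Under Participants, it is a condition of entry that people "have the ability to weigh themselves (e.g. access to scales". No weighing by staff is described.

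On blinding, Randomisation and allocation concealment states that "the participants will be unblinded" and that "some of the secondary outcomes are participant-reported, so participants are also the assessors". For the scans it says: "Staff conducting assessments for some of the secondary outcomes (e.g. body composition) will be blinded". Allocation is revealed once the baseline outcomes are complete.

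Table 3 schedules DXA at baseline and 6 months, without restriction to one arm, for visceral fat, total fat and total lean mass. Data collection and management places the scans at clinics in Melbourne and Sydney. Both fat outcomes are to be given in grams and as a share of total body mass.

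The Diet section sets the diet arm a goal of losing 10% or more of body weight. It also says: "Participants will be asked to weigh themselves at home weekly to record their weight in their logbook".

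**The concern.** Weight is the most direct sign that the diet did what it was meant to do. At 6 months it comes from people who know their arm, and in one arm only they have a numerical goal, a dietitian who reviews progress and a workbook for tracking weight. These are conditions under which reporting error can differ between arms. The direction is not certain. Reporting towards a goal would enlarge the apparent difference, while more practice at weighing could make the diet arm's reports the more accurate ones.

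The plan already brings the same people to a clinic for a blinded scan at the two time points that matter for the 6-month comparison. It gives no reason for preferring self-report there. At stake is the credibility of the between-group weight and BMI difference at 6 months.

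**Working it through.** The plan states no figure on this point, so there is none to reproduce. The check sets the sources side by side and then gives an illustration.

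**Sources by visit**

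| | Baseline | 6 months | 12 months |
|---|---|---|---|
| Weight (Table 3) | self-report | self-report | self-report |
| BMI (source inferred from the abstract) | self-report | self-report | self-report |
| Fat and lean mass (Table 3) | DXA | DXA | none |
| Participant knows allocation | no | yes | yes |

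**What baseline adjustment does.** Write reported weight at 6 months as true weight plus an error with mean e_D in the diet arm and e_E in the exercise arm. Baseline reports precede the reveal of allocation, so their error has the same expectation in both arms. The adjusted between-group difference at 6 months then estimates

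true difference + (e_D − e_E).

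A constant scale offset cancels. This is what the rule of keeping to one set of scales achieves. An error in what is reported after allocation does not cancel if it differs by arm.

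**Whether a total mass is available.** Total fat and total lean mass come from the scan, and fat is expressed relative to total body mass. A total mass is therefore needed at baseline and 6 months. That the scan supplies it is an inference, because the article does not name the source of that denominator.

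**Illustration.** All inputs except the 10% goal are assumptions: baseline weight W of 80 to 100 kg, differential misreport b = |e_D − e_E| of 0.5 to 2 kg, height 1.70 m.

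- As a share of body weight, b/W: 0.5/100 = 0.5% up to 2/80 = 2.5%.
- As a share of a 10% loss, b/(0.10 × W): 0.5/10 = 5% up to 2/8 = 25%.
- In BMI units, b/1.70² = b/2.89: 0.5/2.89 = 0.17 up to 2/2.89 = 0.69.

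These figures only show what an error of the assumed size would do. They are not evidence that such an error occurs.

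**The case against.** The strongest reply has four parts.

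1. **An objective check is already planned.** Visceral and total fat mass by DXA are secondary outcomes at baseline and 6 months. A reader might infer that the trial cannot show objectively whether the diet worked. The documents do not support that, and this part stands.

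2. **Putting DXA into the weight series would do harm.** Statistical analyses puts continuous secondary outcomes measured at all three visits into a mixed model like the primary one, which uses the 6- and 12-month data and adjusts for baseline. There is no scan at 12 months. With DXA at 0 and 6 months and self-report at 12, the change of source would be confounded with the visit. Filling missing scans with self-report would also mix instruments within a visit, possibly unequally by arm. This stands and rules out simply swapping the source within one model. It does not rule out a separate 6-month analysis.

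3. **Baseline reports are not exposed to knowledge of allocation.** This is correct. The scan is still needed at baseline in a DXA analysis, so that both visits share one source.

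4. **The size is assumed, and the outcomes are secondary.** Both are true. The article bases its conclusion on efficacy on the 6-month change in pain. A reader might also infer that a mediation analysis is compromised. The article mentions mediation only as an example for the later analysis plan and names no mediator, so DXA fat mass could serve.

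What remains is that the article fixes a source open to arm-dependent error at a visit where a blinded one is already scheduled.

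**Conclusion.** The point holds as a cheap improvement to a secondary outcome. Self-reported weight and BMI at 6 months are open to reporting error that differs by arm, and baseline adjustment cannot remove it. The size and direction of any such error cannot be derived from the documents. The 5% to 25% of a 10% loss given above rests wholly on the assumed weights and misreporting.

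The conclusion depends on two inferences: that BMI is computed from self-reported weight, and that total mass can be exported from the scans. It concerns the 6-month comparison only. It would be wrong to conclude that the weight result is biased, since the documents show only that it could be, or that the primary pain result is affected, since that outcome does not use weight.

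**What to change.** - Base the 6-month between-group comparison of weight on DXA total mass, adjusted for DXA total mass at baseline. Do the same for BMI, using the height recorded at baseline. Use the scan at both visits, and treat missing scans as missing data without substituting self-report.
- Keep self-reported weight and BMI at 0, 6 and 12 months as their own longitudinal model with no DXA values in it, and take the 12-month result from that model.
- Report self-report minus DXA by arm at baseline and 6 months. This shows directly whether reporting error differs by arm.
- Confirm beforehand that total mass can be exported from the scans held on the server.

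The cost is one additional field per scan, a reworded outcome definition and a second weight analysis to report. No extra visit or procedure is needed. The 12-month result stays self-reported.

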#### Descriptive measures

Descriptive measures include age; body height, sex; duration of symptoms; geographical location; education level; current employment status; problems such as pain, aching discomfort or stiffness in other joints; radiographic disease severity using the Kellgren and Lawrence scale [39]; comorbidities assessed using the Self-Administered Comorbidity Questionnaire [40]; and treatment expectation assessed on a 5-point ordinal scale.

#### Other measures

Other measures will be collected to describe total body lean mass; depression, anxiety and stress [41]; pain-related fear [42], and self-control for eating [43] (Table 3). These measures will not be used to determine treatment efficacy.

### Treatment adherence

At 6 months, participants will report the number of strengthening exercise sessions performed over the prior 2 weeks. At 6 months, adherence to the prescribed physical activity programs, and weight management plan, if applicable, will be self-reported by participants using a 5-point NRS (0 = none of the time; 5 = all of the time). Physiotherapists and dietitians will record the number of attended consultations and the duration of the consultations throughout the 6-months for each participant. The number of weeks participants use meal replacements (diet and exercise group) will also be recorded.

### Adverse events

Adverse events will be defined as any untoward medical occurrence, irrespective of whether it is related to the study interventions or not. Participants are advised to report any adverse events to their study physiotherapist or dietitian as soon as they can. If necessary, treatment is discontinued and further medical advice is arranged. Clinicians are instructed to report any adverse events to the Trial Coordinator and record the event in their consultation notes. Participants are provided with a “help” email address to contact if they have any issues with their exercise/physical activity or weight management program in between consultations. The email is monitored daily by research staff and, if necessary, staff can seek further advice/guidance from the participant’s physiotherapist and/or dietitian. Adverse events will be acquired from participants at 6 and 12 months. Participants are requested to provide details on the nature of the event, if they sought treatment from a doctor or any other health professional, if the event was life-threatening or required hospitalisation, and whether they considered the event related to any component of the intervention they are receiving as part of the study. The Chief Investigator along with other study investigators will determine causality. If the event is related to the trial, it will be deemed a related adverse event. A serious adverse event will be defined as any untoward medical occurrence that; i) results in death; ii) is life-threatening; iii) requires hospitalisation or prolongation of existing inpatients hospitalisation; iv) results in persistent or significant disability or incapacity; v) is a congenital anomaly or birth defect, or; vi) any other important medical condition which, although not included in the above, may require medical or surgical intervention to prevent one of the outcomes listed.

